### Intervention

After baseline assessment (BA1 and BA2), the participants are provided with the different ModuLAAr modules based on their individual interests and housing conditions (e.g. also residents without diabetes are provided with blood glucose meter if wanted; old buildings are equipped with smart home monitoring technology – the ability to control windows or doors is not provided in already existing old buildings). The installed devices will remain in the homes until the projects’ end. After installation, extensive initial system training takes place in the home of the resident. Our aim is that the enrolled study participants have the opportunity to use the system for at least 12 months until the project ends. Within study duration, a follow-up training session after 2–4 months, depending on the individuals’ need for training, is planned. Depending on the point of time of recruitment there will be up to 4 assessment points where technology acceptance and usability will be reviewed. All questionnaires are completed in the course of individual interviews with the residents to address their individual deficiencies if necessary (e.g. the participant is not able to fill in the questionnaires due to cognitive limitations). After the project is completed, the tablet computer will remain property of the resident.

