### Measurements

The study participants are evaluated at 6 points in time: baseline assessment at 4 months (BA1) and 1 month before installation (BA2), 1 month after installation (AP1), after 4 months (AP2), after 12 months (AP3) and if applicable after 18 months or otherwise on project ending (AP4). Not each measurement is used on every point in time. To identify developing trends before intervention the data related to subjective health and QoL between the two baseline assessments (BA1, BA2) are compared to the equal time span of the two assessments points after installation (AP1, AP2). Table 1 summarizes the planned measurements at several times (BA1, BA2, AP1, AP2, AP3, AP4) in the study population.

**Table 1 T1:** Questionnaires and qualitative assessment methods in ModuLAAr

	**BA1 (−4 months)**	**BA2 (−1 months)**	**AP1 (1 month)**	**AP2 (4 months)**	**AP3 (12 months)**	**AP4 (18 months)**

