### Statistical analysis

Analyses will be conducted using SPSS® version 21.0 (SPSS Corp, Chicago, Illinois, USA) and Microsoft Excel 2010® software. Descriptive statistics and interferential statistics are performed. The sample data is carried out by frequencies or percentages, means, standard deviation, and graphics. Descriptive statistics are used to summarize demographic parameters and baseline data. General Linear Models (ANCOVA) controlling for baseline performance and other confounding variables is used if required. The delta-outcome of the baseline assessments (delta of BA1 to BA2) will be compared to the iterative delta of the data gathered by the intervention assessment (e.g. delta of AP1 to AP2, delta of AP1 to AP3) of each participant. To partially overcome the limitation of the lack of having a control group in the interim project analysis, the outcome data of the evaluated study population (delta of AP1 to AP2) is compared to those participants who finished the baseline assessment at that point in time (the same month) but are not yet provided with an installed system. All tests are two-sided at a significance level of p <0.05. T-test is used to compare baseline data and data of the follow-ups. Pearson and Spearman correlation coefficients are used for confounder identification. For the case that normal distributions couldn’t be reached non parametric tests (Wilcoxon, Mann-Whiteney-U-Test) are used in combination with Spearman and Kendall´s tau correlation coefficients.

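### The 3-month baseline change is compared with longer, unequal follow-up changes without scaling for time; for quality of life this affects AP4, whose date varies

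*Protocol article*

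**What the plan says.** The Measurements section of the protocol article sets the "baseline assessment at 4 months (BA1) and 1 month before installation (BA2") and the follow-up at "1 month after installation (AP1), after 4 months (AP2), after 12 months (AP3"). The last visit takes place "if applicable after 18 months or otherwise on project ending (AP4"). To separate the effect from trends already under way, the BA1 to BA2 data on quality of life and subjective health are "compared to the equal time span of the two assessments points after installation (AP1, AP2").

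The Statistical analysis section compares each participant's BA1 to BA2 change with a series of follow-up changes, given by example as "delta of AP1 to AP2, delta of AP1 to AP3". It mentions no division by elapsed time. ANCOVA is to be used only where needed, and time is not among the covariates it names.

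The Intervention section makes follow-up depend on entry date: "Depending on the point of time of recruitment there will be up to 4 assessment points". It also states an aim that residents "have the opportunity to use the system for at least 12 months until the project ends".

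Table 1 schedules WHOQOL-BREF, WHOQOL-OLD and EQ5D-VAS at BA1, BA2, AP1, AP2 and AP4. Their AP3 cells are empty.

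**The concern.** A before-and-after comparison of changes removes a background trend only if both windows have the same length. The Measurements section relies on exactly that for AP1 to AP2. The Statistical analysis section then carries the comparison to longer windows, where the condition fails. A longer window collects more natural change than a 3-month one, so the hypothesis of equal changes is false under any steady trend, even if the system does nothing.

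The abstract makes change in quality of life and subjective health across the study duration the primary outcome. After month 4 the only visit with these instruments is AP4. The one long-term comparison available for the primary outcomes therefore has the most unequal windows, and its length also differs between residents.

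**Working it through.** **Inputs.** From the Measurements section, in months from installation: BA1 −4, BA2 −1, AP1 +1, AP2 +4, AP3 +12, AP4 +18 or project end. From the Intervention section: an aim of at least 12 months of use, so AP4 lies between about month 12 and month 18 if the aim is met.

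**Step 1: the plan's own statement of equal spans.** BA1 to BA2: −1 − (−4) = 3 months. AP1 to AP2: 4 − 1 = 3 months. The equality is reproduced.

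**Step 2: the longer spans.** AP1 to AP3: 12 − 1 = 11 months, 3.67 times the baseline span. AP1 to AP4: 18 − 1 = 17 months, 5.67 times the baseline span, or 12 − 1 = 11 months if AP4 falls at month 12.

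**Step 3: which changes can be formed.** In Table 1 only WHOQOL-BREF, WHOQOL-OLD and EQ5D-VAS are measured at both BA1 and BA2, and none of them is measured at AP3. The AP1 to AP3 example therefore cannot be set against the baseline change for any instrument. AP1 to AP2 and AP1 to AP4 can be.

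**Step 4: expected difference with no system effect.** For a steady trend of r per month:

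follow-up change − baseline change = r × span − r × 3 = r × (span − 3)

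This gives 0 for AP1 to AP2, 14r for AP1 to AP4 at month 18, and 8r if AP4 is at month 12. For assumed declines of 0.1, 0.25 and 0.5 points per month on a 0–100 scale, the spurious difference is −1.4, −3.5 and −7.0 points at 17 months, and −0.8, −2.0 and −4.0 at 11 months.

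**Step 5: chance of p < 0.05 with no system effect.** The article gives no trend, SD or correlation, so these are assumptions: all 50 residents measured, common SD of 1, common within-person correlation ρ = 0.7, and a two-sided paired test by normal approximation. The variance of the difference between the two changes is 4(1 − ρ) = 1.2, so SE = √1.2/√50 = 0.155. For a decline of 0.2 SD per year at 17 months, the shift is 0.2/12 × 14 = 0.233, the ratio to SE is 1.51, and the chance is Φ(−1.96 + 1.51) plus a negligible term, about 33%.

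| Assumed decline per year | AP1 to AP2 (3 months) | AP4 at month 12 (11 months) | AP4 at month 18 (17 months) |
|---|---|---|---|
| 0.1 SD | 0; 5% | −0.07 SD; 7% | −0.12 SD; 12% |
| 0.2 SD | 0; 5% | −0.13 SD; 14% | −0.23 SD; 33% |
| 0.3 SD | 0; 5% | −0.20 SD; 25% | −0.35 SD; 62% |

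Across ρ from 0.6 to 0.8 the 17-month figures run from about 10% to 79%. With 35 residents and ρ = 0.7 they are about 10%, 24% and 47%.

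**Step 6: what time scaling can and cannot do.** Dividing each change by its months gives r − r = 0, so a linear trend cancels. Precision stays poor. With independent measurement error σ per visit, one resident's baseline rate has SD √2σ/3 = 0.47σ per month, against √2σ/17 = 0.08σ for AP1 to AP4, so the short baseline dominates. Projecting one resident's two baseline points to month 18, which is 19 months after BA2, gives 7.33 × BA2 − 6.33 × BA1. Observed minus projected then has SD √(7.33² + 6.33² + 1)σ ≈ 9.7σ, against √2σ ≈ 1.4σ for a simple change.

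**The case against.** The strongest reply is that the only long follow-up change named in the analysis text is AP1 to AP3, which Table 1 makes impossible for these instruments, and that AP1 to AP4 is never named. The first part is right, and it moves the problem to AP4. The second has some force, but the changes are given as examples of a series that runs through follow-up. With a primary outcome defined across the study duration, AP1 to AP4 is the natural reading.

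It can also be said that visit windows and timing covariates are often left to an analysis plan, and that the article describes the study as explorative and warns that causality is uncertain. This lowers the stakes without removing the point. The article does state a comparison, and that comparison conflicts with its own equal-span rationale. The caveat in the Discussion concerns the missing control group. The same-month comparison with residents not yet equipped covers only AP1 to AP2 at the interim analysis.

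A reader might infer more than the article supports:

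- **That the whole comparison of changes is biased.** AP1 to AP2 is matched and is unaffected.
- **That decline would create a false benefit.** It would show as harm or mask a benefit. Only a rising baseline trend would favour the system.
- **That decline is certain because residents need care.** The Study design section says they need not be dependent, and no rate is given.
- **That the plan pools all AP4 values as 18-month data.** Table 1 heads the column that way, but no sentence says so, and the Measurements section openly allows project end.

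**Conclusion.** The point holds for the long-term comparison of quality of life and subjective health at AP4. The protocol article's own schedule sets a 3-month change against one of up to 17 months, varying between residents, with no stated allowance for time. The factors 14r and 8r follow from the visit times and assume only a steady trend. The differences in points or SD and the chances of significance rest on assumed rates, and the chances also on an assumed correlation and number measured; they illustrate scale and do not predict the result. Separately, the Statistical analysis section names an AP1 to AP3 change that Table 1 gives no data to form for these outcomes, and the two must be reconciled. Both matters should be settled before the AP4 data are analysed.

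**What to change.** 1. Restrict the raw comparison with BA1 to BA2 to the matched AP1 to AP2 change.
2. For AP4, compare change per month, or fit a model with actual months since installation as the time variable. The article specifies no such model, so this would be an addition.
3. Record the actual AP4 date for each resident, report its distribution, and do not treat all AP4 data as 18-month data.
4. Reconcile the AP1 to AP3 example in the Statistical analysis section with the empty AP3 cells in Table 1.
5. Report the long-term comparison as exploratory, and state that it assumes a linear trend estimated imprecisely from a 3-month baseline. Do not project individual two-point baseline trends to month 18.

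The cost is a few sentences in the plan and a little more analysis work, with no added visits or instruments. The price is wide uncertainty in the time-scaled AP4 result: scaling removes the bias from a linear trend but cannot make a 3-month baseline informative about 17 months.

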## Methods/Design

### Overview

ModuLAAr is a research project approved and funded by the benefit-program of the Austrian Research Promotion Agency (FFG) and the Austrian Federal Ministry of Transport, Innovation and Technology (BMVIT). The main objective of the project is to equip up to 50 flats with an AAL solution that will be adapted according to the individual needs of the residents in assisted living homes. Those already existing homes as well as new built ones will be considered for integration of the different AAL-modules. The new buildings are located in 3 and the existing homes in 6 municipalities. People living in assistive living homes provided by the Samariterbund Burgenland Rettung und Soziale Dienste GmbH may be considered for participation within the project.

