### Study design

To establish a practical study design for the given framework of the whole project, a quasi-experimental longitudinal study with pre- and post-tests is conducted to evaluate the impact of the different AAL modules within the study population. For the study 50 persons aged 60 and older are recruited who will receive the module-based AAL solution. Those people are not necessarily dependent elderly, they live in the assisted living accommodations with an option to get support of service and nursing staff when needed or wanted. The effects of ModuLAAr are evaluated at 1-, 4, 12 and 18-months follow-ups by comparing the quantitative and qualitative results to the outcome of 2 baseline assessment points. An overview of the study design and the assessment points is provided in Figure 1. Beside the requirements of the project´s consortium members the heterogeneous combination of technical appliances, which are adapted according to the housing conditions of the participants, the creation of a control group is not appropriate to evaluate potential impacts on the study population of this specific project.

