### ModuLAAr system

The system is based on a flexible and scalable home server architecture named Homer Platform [11] developed by the AIT Austrian Institute of Technology GmbH. User interface are tablet computers with a pre-loaded software application. Furthermore, a software platform will be provided to share data between the residents and their relatives or social services.

To address the building conditions, the new built homes are equipped in construction phase with a cable bound infrastructure and a centralized installation of the server; already existing houses will be adapted with wireless technologies and decentralized installation of mini-computers.

The ModuLAAr system consists of technologies and services which are applied in four module-domains (Figure 2) which correlate with the health and QoL domains which shall be impacted [9]:

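### The interim comparison with residents still waiting for the system starts one month after installation, so it cannot detect an effect that arises early and then holds

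*Protocol article*

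**What the plan says.** Under Study design, the protocol article describes a quasi-experimental pre-post study in which every recruited resident receives the system, and states that "the creation of a control group is not appropriate to evaluate potential impacts on the study population of this specific project". Under Statistical analysis it offers a substitute, introduced with "To partially overcome the limitation of the lack of having a control group in the interim project analysis". The substitute takes "the outcome data of the evaluated study population (delta of AP1 to AP2". This change "is compared to those participants who finished the baseline assessment at that point in time (the same month", with the further condition that they have completed baseline "but are not yet provided with an installed system".

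The visit times are under Measurements: "baseline assessment at 4 months (BA1) and 1 month before installation (BA2), 1 month after installation (AP1), after 4 months (AP2". The same section says that the BA1-to-BA2 and AP1-to-AP2 intervals are of equal length. Elsewhere in Statistical analysis, each participant's baseline delta is compared with deltas that start at AP1, a t-test compares baseline with follow-up data, and ANCOVA is available for confounders if required. Recruitment is up to 50 residents.

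**The concern.** A comparison with people still waiting is useful because it removes calendar and seasonal drift from the effect of getting the system. To do so, the treated change has to span the moment of getting it. Here it begins at AP1, when the system has been in place for a month.

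No other planned test closes the gap. The within-person delta comparison also starts at AP1. The t-test of baseline against follow-up does cross installation, but has no concurrent comparison group. So the test that can see the step is uncontrolled, and the controlled test cannot see the step. The abstract names change in quality of life and subjective health across the study as primary, so an early sustained benefit or harm could pass through the interim comparison as no difference.

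The waiting group adds two weaknesses. Nothing in the article fixes who is equipped early and who waits, and the matching rule may leave few controls.

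**Working it through.** **Intervals, from the Measurements section**

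- BA1 to BA2: -1 - (-4) = 3 months.
- AP1 to AP2: 4 - 1 = 3 months. The stated equality of the two spans is reproduced.
- BA2 to AP1: 1 - (-1) = 2 months. This is the stretch left out; it holds installation, initial training and the first month of use.
- BA2 to AP2: 4 - (-1) = 5 months.

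**What the contrast estimates**

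Let g be the drift over the shared three calendar months and E(m) the effect m months after installation. I read the waiting residents' outcome as their BA1-to-BA2 change, which the equal-span statement implies.

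- Installed: g + E(4) - E(1)
- Waiting: g
- Difference: E(4) - E(1)

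If E(1) = E(4), the difference is 0 whatever the sample size. Covariate adjustment does not restore a change that took place before AP1.

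**Share of the month-4 effect that remains visible**, [E(4) - E(1)] / E(4). The curves are assumptions; the article gives none.

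| Onset of effect | Share seen from AP1 to AP2 |
|---|---|
| Complete by month 1, then flat | 0% |
| Exponential, time constant 0.5 months | 14% |
| Exponential, 1 month | 36% |
| Exponential, 2 months | 54% |
| Exponential, 4 months | 65% |
| Linear from installation | 3/4 = 75% |

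For the exponential, E(m) = 1 - exp(-m/T). With T = 1: E(1) = 0.63, E(4) = 0.98, and (0.98 - 0.63)/0.98 = 0.36.

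**Precision**

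The article gives no SD, effect size or number waiting. I work in units of the SD of the change score, two-sided 0.05, normal approximation, with all 50 residents in one group or the other. That is generous, since some will be at other visits.

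SE = sqrt(1/w + 1/(50 - w)), with w waiting. Power for 0.5 SD fully visible is about Phi(0.5/SE - 1.96). The difference detectable with 80% power is (1.96 + 0.84) x SE.

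| Waiting / installed | SE | Power for 0.5 SD | Detectable difference |
|---|---|---|---|
| 5 / 45 | 0.47 | 18% | 1.32 SD |
| 10 / 40 | 0.35 | 29% | 0.99 SD |
| 15 / 35 | 0.31 | 37% | 0.86 SD |
| 25 / 25 | 0.28 | 42% | 0.79 SD |

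The 42% at 25 versus 25 falls to 26% if three quarters of the effect is visible (0.375 SD), and to 5%, the significance level, if the effect is complete by AP1.

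**Non-random waiting group**

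Because both sides are change scores, stable differences between the groups cancel and only different trends bias the result. With no true effect, a trend difference of 0.3 SD (assumed) gives a rejection probability of 14% at 10 versus 40 and 19% at 25 versus 25, instead of 5%.

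**The case against.** The protocol is modest about this comparison. It promises only to offset the missing control group in part, and only at the interim. The Discussion concedes that causality cannot be assured, calls the study explorative and recommends a control arm for later trials. Equal spans and same-month matching are deliberate and do help against season. Follow-up training at 2 to 4 months falls within AP1 to AP2, so some effect may arise there. Level change is examined by the baseline versus follow-up t-test. All of this stands. None of it lets the concurrent comparison see a change that occurred before AP1, and the general caveat on causality does not tell the reader about that blind spot.

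A reader might infer more than the article supports:

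- **That building type decides who waits.** The article says that "already existing houses will be adapted with wireless technologies and decentralized installation of mini-computers", while new homes are cabled during construction, and that "The new buildings are located in 3 and the existing homes in 6 municipalities". This ties equipment to building, not order of installation. The only timing factor mentioned is when a resident is recruited. Building may play a role, but this is not stated.
- **That only a handful of controls can exist.** Spreading 50 installations evenly over 12 months would give about four a month (50/12 = 4.2), but no roll-out schedule is given. If whole homes are equipped together, many residents could share a month.
- **That the same resident serves as control and as treated in one test.** This arises only if successive months are pooled, which the article does not say.
- **That the comparison is blind to every effect.** It is fully blind only to one that is complete by month 1 and then flat.

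It can also be said that a mixed model would not cure non-random order, and that a rich one is unlikely to be estimable with 50 people. That is right, and it limits the remedy.

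**Conclusion.** The concern holds in a limited form. From the visit schedule alone, the interim contrast estimates E(4) - E(1). It has expectation zero for an effect that arises by month 1 and is held, and captures only part of a gradual one. For an early sustained effect it does not replace a control group even partially.

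The 14% to 75% range rests on assumed onset curves, and the 18% to 42% power on an assumed 0.5 SD effect and assumed group sizes. Lack of randomisation and of a stated installation order is a second, lesser weakness whose bias cannot be sized from the article. That matching leaves few controls is possible but not established.

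The point should be acted on, because assessments already scheduled allow a contrast that includes the missing step.

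**What to change.** At interim and final analysis, replace the comparison with one small mixed model per WHOQOL scale and for the EQ VAS. Use every assessment at which Table 1 schedules them: BA1, BA2, AP1, AP2 and AP4 (none is planned at AP3). Include calendar time in few terms, a time-varying indicator for system installed, building type and a random resident effect; add a home effect only if it can be estimated. The change from BA2 to AP1 is then judged against residents still waiting at the same calendar time.

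Report the result as a non-randomised estimate that assumes similar underlying trends in early and late residents, and show how many residents were waiting at each calendar period. Assessments taken after the last installation have no waiting residents beside them, and a single indicator averages the effect over follow-up visits; both limits should be stated. Simply starting the treated change at BA2 is not enough: it would span 5 months against the waiting group's 3.

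No new data collection is needed beyond the assessment and installation dates. The cost is modest analysis work and reliance on the trend assumption. Drawing the order of homes by lot is not required.

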**Methods/Design:**

A treatment group of adults aged 60 years and older will be recruited within the participating assisted living homes. At baseline, the participating volunteers will report on quality of life, subjective health and sociodemographic conditions. After system installation, prospective follow-up (1, 4, 12 and 18 months) with additional reporting on technology acceptance and usability of the system will be conducted. Mixed methods data collection, linking quantitative data to interview-gathered qualitative data will be applied. Primary outcome measure will be the change in quality of life and subjective health across study duration.

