### Study objectives

The study aims to evaluate the provided ambient assisted living solutions by measuring the changes in QoL, subjective health and technology acceptance. The primary objective of this study is to increase the domain specific QoL of the involved residents by this intervention, measured with a mixed-method approach which takes into account quantitative as well as quantitative information.

It is proposed to increase social integration due to the provided technical solutions which will have impact on interaction with other residents and relatives. Further objective of the study is to improve resident´s knowledge of the individual health status and thereby have positive effects on health behavior.

Furthermore the results shall identify the key facts how technology acceptance for AAL solutions can be enhanced and influenced.

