**Other measurements**						
Sociodemographic Parameters	●					
Health threatening event in the past	●			●		●
Support for limitations	●			●		●

For evaluation of the outcomes a mixed-method approach with qualitative and quantitative methods is applied. Because of the heterogeneous combinations of technologies and participants, this modus operandi will provide the ability to gather additional information for qualitative analysis to the data collected for quantitative analysis.

Following measurements are performed:

Measurement for eligibility screening:

• MMSE: Cognitive function assessed by the German version [12] of the Mini Mental State Examination [13]

Measurements of health status and QOL:

• WHOQOL-BREF [14]: German version of the short form of the World Health Organization Quality of Life Questionnaire (Question nr. 21 was omitted due to the concerns of the consortium members)

• WHOQOL-OLD [15]: German version of the World Health Organization Quality of in the Elderly Questionnaire (Domains: “sensory”, “functions”, “autonomy”, “activities in the past, present and future”)

• EQ-5D VAS [16]: German Version of the Euroqol Visual Analogue Scale from the EQ-5D Quality of Life Questionnaire (The EQ-5D Questions 1–5 were omitted due to the concerns of the consortium members)

• Health and Quality of Life - Interviews: Semi-structured qualitative interviews and focus groups according to the bio-psycho-social model of Engel [17] and the multidimensional QOL-approach of the WHO [18]

Measurements of technology acceptance and usability:

• TAEG [19]: “Measuring technology affinity” questionnaire of the Technical University of Berlin.

• USABILITY Questionnaire developed by the usability competence team of the FH Technikum Wien based on: The System Usability Scale (SUS) [20], User Experience Questionnaire (UEQ) [21] and Microsoft Product Reaction Cards® [22]

• Technology acceptance - Interviews: Semi-structured qualitative interviews and focus groups according to the models of McCreadie&Tinker [23] for assistive technology for older people and the technology acceptance model(TAM) of Davis [24]:

• Perceived satisfaction question: “How many points you would give us for the ModuLAAr System?” (5-point Likert scale; AP2, AP4)

• Technology estimates:

What are your general estimates regarding the different modules (of the previous presentation)?” (open format, only at BA1)

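### A flat 5% level on all tests, with no decisive score, time point or contrast for the primary outcome, does not hold the error rate of the primary claim at 5%

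*Protocol article*

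**What the plan says.** The abstract states: "Primary outcome measure will be the change in quality of life and subjective health across study duration". This names two constructs but no instrument, score or time point. The Study objectives section states: "The primary objective of this study is to increase the domain specific QoL of the involved residents by this intervention". This works at domain level and does not repeat subjective health, although the sentence before it lists subjective health among the changes to be measured.

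Three instruments serve these constructs in the Measurements section:
- WHOQOL-BREF: "German version of the short form of the World Health Organization Quality of Life Questionnaire", with no number of domains given.
- WHOQOL-OLD: "Domains: “sensory”, “functions”, “autonomy”, “activities in the past, present and future".
- EQ-5D VAS: "German Version of the Euroqol Visual Analogue Scale from the EQ-5D Quality of Life Questionnaire", one score.

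Table 1 schedules all three at BA1, BA2, AP1, AP2 and AP4, and none of them at AP3.

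For testing, the Statistical analysis section compares the BA1-to-BA2 change with the "iterative delta of the data gathered by the intervention assessment (e.g. delta of AP1 to AP2, delta of AP1 to AP3) of each participant". It adds: "T-test is used to compare baseline data and data of the follow-ups". It also plans an interim comparison with residents who are not yet equipped, and ANCOVA when needed. The level is fixed once, for everything: "All tests are two-sided at a significance level of p <0.05". The Measurements section singles out one comparison for quality of life and subjective health, BA1–BA2 against the equally long AP1–AP2 interval, but does not call it primary.

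**The concern.** A 5% test protects a claim at 5% only if the claim rests on one test, or on several that are jointly controlled. Here the primary claim, that quality of life or subjective health changed, could be supported by any one of several scores at any one of several contrasts, each judged at 5%. The article sets no order among them. The abstract and the objectives also differ on how wide the primary outcome is, so a reader of the results could not tell whether a significant VAS, or a single significant domain, counts as a primary finding. At stake is how a single significant result from a one-group study of up to 50 people may be read.

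**Working it through.** **The plan's own figure.** The article gives no power calculation and no overall error rate. The only figure is the per-test level of 0.05, so there is nothing further to reproduce.

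**Number of scores.** This is partly an assumption, so three counts are used:
- 3 scores: one total per instrument.
- 5 scores: a WHOQOL-BREF total, three WHOQOL-OLD domains and the VAS (1 + 3 + 1).
- 8 scores: four WHOQOL-BREF domains (assumed, not in the article), three WHOQOL-OLD domains and the VAS (4 + 3 + 1).

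The WHOQOL-OLD list as printed has four labels. It gives three domains if the first two belong together; counting four would add one score to the second and third cases.

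**Number of contrasts feasible under Table 1.**
- Delta versus delta, each against BA1–BA2: AP1–AP2 and AP1–AP4, which makes 2. AP1–AP3 is named in the text but cannot be formed for these instruments, so it is not counted.
- Baseline versus follow-up: AP1, AP2 and AP4, which makes 3.

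The total is 5. The interim comparison, ANCOVA and the open choice between BA1 and BA2 as baseline are left out, so the count is conservative for a reader who tests everything the section allows.

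**Independent tests.** The chance of at least one p<0.05 among m tests with no effect is 1 − 0.95^m.
- One contrast: m = 3 gives 14%, m = 5 gives 23%, m = 8 gives 34%.
- Five contrasts: m = 15 gives 54%, m = 25 gives 72%, m = 40 gives 87%.

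These are too high for this design, because the scores come from the same people and the contrasts share assessments.

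**Correlated tests.** A simulation with no effect used paired t-tests, 50 complete cases, 3,000 runs, a correlation of 0.6 within a score over time, and correlations of 0 to 0.7 between scores. The correlations are assumptions. BA2 served as baseline for the t-tests. The one-contrast column is BA1–BA2 versus AP1–AP2.

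| Scores | One contrast, either direction | Five contrasts, either direction | Five contrasts, favourable direction |
|---|---|---|---|
| 3 | 11–15% | 35–45% | 18–24% |
| 5 | 16–23% | 45–64% | 24–39% |
| 8 | 20–33% | 54–78% | 30–52% |

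Within each range, the lower end belongs to the highest between-score correlation. Simulation error is at most about 0.9 percentage points (√(0.5 × 0.5 / 3000) = 0.009). With 30 complete cases the results were similar, for example 34–44% for 3 scores and 54–80% for 8 scores over five contrasts.

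**After a fix.** One named score at one contrast has an error rate of 5%. With Holm across 8 scores at one contrast, the smallest p-value is compared with 0.05/8 = 0.00625, and the family-wise rate is at most 5%.

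**The case against.** Four points can be made for the plan.

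First, the study describes itself as explorative. Its Discussion accepts that differences between baseline and post-test may not be caused by the project, and quantitative results are to be set beside interviews and focus groups. This stands as a reason to lower the severity. It does not answer the point: the causal caveat concerns the missing control group, triangulation does not control an error rate, and the article still names a primary outcome and plans significance tests on it.

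Second, a multiplicity procedure and a list of tests are often left to an analysis plan, which is not shown here. This stands in part. A reader might infer that every score will be tested at every contrast; the article does not list the tests and does not say so. What it does state is a level for all tests, and it states the primary outcome without a decisive score or contrast. The point rests on those statements.

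Third, a reader might infer that a significant primary result is likely even if the system does nothing. That goes too far. The chance exceeds 50% in either direction only on some combinations of scores, contrasts and correlation. It is 11–33% at one contrast, and a false result in the favourable direction mostly stays below 50%.

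Fourth, the abstract gives an outcome measure and the objectives section an objective, so the difference between them is a mismatch in scope. That is fair: it calls for alignment, and it does not show that results will be selected after the data are seen.

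**Conclusion.** The point holds in moderate form. As written, the stated 5% level does not apply to the primary claim. With no effect, the chance of at least one p<0.05 in either direction is about 11–33% for 3 to 8 scores at a single contrast, and about 35–78% for the same scores over five contrasts. These ranges rest on an assumed number of WHOQOL-BREF scores, on assumed correlations, and on the reader counting all five contrasts as evidence on the primary outcome. Even the narrowest case, three totals at one contrast, is at least twice the nominal level. Because the study is exploratory and uncontrolled by its own account, this should be corrected but does not undermine the study as a whole.

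**What to change.** 1. Make the abstract and the Study objectives section agree on whether subjective health is part of the primary outcome.
2. Name as primary the contrast that the Measurements and Statistical analysis sections already describe: change from BA1 to BA2 versus change from AP1 to AP2.
3. At that contrast, either name one primary score, or apply Holm's procedure across the quality-of-life domain scores and the VAS, and list those scores.
4. Report all other contrasts, including those to AP4, the baseline-versus-follow-up comparisons and the interim comparison, as estimates with 95% confidence intervals and no significance claims.

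The cost is wording in three places, and no new assessment is needed. The downside is that fewer results can be called significant. The chosen contrast also measures change between 1 and 4 months after installation, so a shift that is complete by AP1 would not show in it; the BA2-to-follow-up estimates under step 4 keep such a shift visible.
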